## Abstract

**Background:**

Approximately 20 % of hepatocellular carcinoma (HCC) patients diagnosed in the early stages may benefit from potentially curative ablative therapies such as surgical resection, transplantation or radiofrequency ablation. For patients not eligible for such options, prognosis is poor. Sorafenib and Selective Internal Radiation Therapy (SIRT) are clinically proven treatment options in patients with unresectable HCC, and this study aims to assess overall survival following either SIRT or Sorafenib therapy for locally advanced HCC patients.

**Methods:**

This investigator-initiated, multi-centre, open-label, randomized, controlled trial will enrol 360 patients with locally advanced HCC, as defined by Barcelona Clinic Liver Cancer stage B or stage C, without distant metastases, and which is not amenable to immediate curative treatment. Exclusion criteria include previous systemic therapy, metastatic disease, complete occlusion of the main portal vein, or a Child-Pugh score of >7. Eligible patients will be randomised 1:1 and stratified by centre and presence or absence of portal vein thrombosis to receive either a single administration of SIRT using yttrium-90 resin microspheres (SIR-Spheres®, Sirtex Medical Limited, Sydney, Australia) targeted at HCC in the liver by the trans-arterial route or continuous oral Sorafenib (Nexavar®, Bayer Pharma AG, Berlin, Germany) at a dose of 400 mg twice daily until disease progression, no further response, complete regression or unacceptable toxicity. Patients for both the Sorafenib and SIRT arms will be followed-up every 4 weeks for the first 3 months and 12 weekly thereafter. Overall survival is the primary endpoint, assessed for the intention-to-treat population. Secondary endpoints are tumour response rate, time-to-tumour progression, progression free survival, quality of life and down-staging to receive potentially curative therapy.

**Discussion:**

Definitive data comparing these two therapies will help to determine clinical practice in the large group of patients with locally advanced HCC and improve outcomes for such patients.

**Trial registration:**

ClinicalTrials.gov identifier, NCT01135056, first received 24, May 2010.

## Background

The incidence and prevalence of hepatocellular carcinoma (HCC) is highly variable in different regions of the world, but the burden is predicted to increase in future years [1]. Approximately 70–80 % of all cases of HCC occur in Asia where it is an important public health concern [2]. Although around 20 % of patients diagnosed with early stage HCC may benefit from potentially curative ablative therapies, such as surgical resection, liver transplantation or radiofrequency ablation [3–5], most patients are diagnosed at an intermediate to advanced stage of HCC, when treatment options are limited and the prognosis poor [6, 7]. In patients with untreated advanced HCC median survival time is approximately 5–7 months, although this varies depending on the Child‐Pugh score [8–10].

The only systemic therapy shown to confer survival advantage in patients with unresectable advanced HCC is Sorafenib (Nexavar®, Bayer Pharma AG, Berlin, Germany) [11–13]. In the pivotal Sorafenib Hepatocellular Carcinoma Assessment Randomized Protocol (SHARP) trial in patients with advanced HCC, Sorafenib treatment significantly increased median overall survival (OS) by 2.8 months versus placebo (10.7 months versus 7.9 months, respectively; *p* < 0.001) [6]. A subsequent randomised controlled trial in the Asia-Pacific region confirmed these findings, showing median OS of 6.5 months with Sorafenib treatment versus 4.2 months with placebo (*p* < 0.014) [13]. As a result of these data, Sorafenib is the current recommended first-line treatment for advanced (Barcelona Clinic Liver Cancer [BCLC] stage C) HCC [2]. Effective systemic therapy is an important option for the treatment of HCC in the subset of patients with extrahepatic metastases and Sorafenib resulted in a median OS of 5.7 months in this group [14]. However, the relative benefits of Sorafenib and loco-regional ablative therapy are unclear in the larger group of patients with locally advanced HCC. This is of critical importance since HCC is a fast-growing locally aggressive disease frequently leading to the patient’s death before extrahepatic metastases have developed. Consequently, the response of loco-regional disease to first-line therapy determines survival in these patients.

Selective Internal Radiation Therapy (SIRT) with yttrium-90 (Y-90) resin microspheres (SIR-Spheres®; Sirtex Medical Limited, Sydney, Australia), is one potential alternative treatment for locally advanced HCC. SIRT enables targeted delivery of radiation to the tumours, while largely sparing the surrounding liver parenchyma. A meta‐analysis showed a high response rate to Y-90 SIRT in HCC patients [15]. Population disparity prevented assessment of OS in this meta-analysis, but cohort studies of patients with HCC receiving SIRT report median OS between 7.0 and 26.3 months [16–25].

Small-scale, retrospective studies have compared SIRT with Y-90 resin microspheres and Sorafenib, and suggest similar median OS in patients with BCLC stage B or C disease [24, 26, 27], and there are some indications that in patients with locally advanced HCC and portal vein thrombosis (PVT), SIRT is particularly beneficial [14, 22, 27–29].

However, larger-scale studies are needed to assess this comparison, and therefore, the Selective Internal Radiation Therapy versus sorafeNIB (SIR*ve*NIB) trial has been designed as a prospective, randomized, open-label, multicentre trial to compare median OS in patients with locally advanced HCC receiving either SIRT with Y-90 resin microspheres or Sorafenib.

Another large-scale comparative study of similar design in patients with advanced HCC, SorAfenib versus Radioembolisation in Advanced Hepatocellular carcinoma (SARAH), is ongoing in Europe [30], and these two studies could potentially be combined in a future meta-analysis.

## Methods/Design

### Ethics

The SIR*ve*NIB trial will be conducted in accordance with the Declaration of Helsinki and current Good Clinical Practice guidelines, and all participating centres will have obtained the relevant ethics committee approval before patient enrolment.

### Eligible population

The inclusion and exclusion criteria for the SIR*ve*NIB trial are summarised in Table 1. Informed consent will be obtained from each participant.

**Table 1 Tab1:** Patient eligibility criteria for SIR*ve*NIB trial

Inclusion criteria	Exclusion criteria
• Unequivocal diganosis of locally advanced HCC without extrahepatic metastases • Written informed consent provided • Aged ≥18 years • Patients with HCC that is not amenable to surgical resection, immediate liver transplantation, or that could be treated with local ablative techniques (e.g. radiofrequency ablation) • Locally advanced HCC as defined by BCLC (B) intermediate stage or BCLC (C) advanced stage • At least one lesion that can be accurately measured in at least one dimension (longest diameter to be recorded) as ≥10 mm with spiral CT scan or MRI • ECOG performance status 0–1 • Adequate haematological function: haemoglobin ≥9.5 g/dl, leukocytes ≥2500/mm^3^, platelets ≥80,000/mm^3^, INR ≤2.0 • Adequate kidney function: creatinine <2.0 mg/dl • Adequate hepatic function: albumin ≥2.5 g/dl, bilirubin ≤2 mg/dl; ALP, AST or ALT ≤5 x ULN • Liver cirrhosis Child-Pugh A–B (up to 7 points) • Life expectancy of at least 3 months without active treatment	• Patients who have had >2 administrations of hepatic artery directed therapy • Hepatic artery directed therapy <4 weeks before study entry • Systemic chemotherapy for HCC, except previous adjuvant or neoadjuvant therapy given >6 months before enrollment • Previous treatment with Sorafenib or VEGF inhibitors • Previous radiotherapy for HCC or other malignancy • Intractable ascites, or other clinical signs of liver failure • Complete thrombosis of the main portal vein • Extrahepatic metastases, except lung nodules <1 cm or local-regional lymph nodes <2 cm in greatest diameter • Clinical signs of central nervous system metastases • Other concurrent malignancy, except for adequately treated basal cell or squamous cell skin cancer, in situ cervical cancer, or other cancer for which the patient has been disease free for ≥5 years • Uncontrolled intercurrent illness • Contraindications angiograghy to hepatic artery catheterisation: severe peripheral arterial disease precluding catheterisation, bleeding diathesis not correctable by standard forms of therapy, portal hypertension with hepato-fugal flow • History of allergy to SIR-spheres, Soranefib or related agents • Patient unable or unwilling to understand or sign the written informed consent • Currently enrolled in another investigational therapeutic drug or device study • Women, unless postmenopausal or surgically sterile are unwilling to practice effective contraception • Men unwilling to use effective contraception during the course of the study

*ALP* alkaline phosphatase, *ALT* alanine aminotransferase, *AST* aspartate transaminase, *CT* computed tomography, *MRI* Magnetic resonance imaging, *ECOG* Eastern Cooperative Oncology Group, *HCC* hepatocellular carcinoma, *INR* international normalised ratio, *ULN* upper limit of normal

### Overview of trial design

SIR*ve*NIB is a prospective, randomized open-label, multicentre trial comparing SIRT and Sorafenib in patients with locally advanced HCC. In SIR*ve*NIB, the aim will be to recruit a minimum of 360 patients from a minimum of 15 sites across the Asia-Pacific region.

Eligible patients will be randomized 1:1 to receive either systemic therapy with oral Sorafenib or a session of SIRT with SIR-Spheres® (Fig. 1). Randomisation will be stratified by centre and the absence or presence of PVT.

**Fig. 1 Fig1:**
[figure not shown]
Overview of the SIR*ve*NIB trial design. ECOG, Eastern Cooperative Oncology Group; PVT, portal vein thrombosis

### Treatment

Treatment in the Sorafenib arm will commence within 1 week after randomisation. Patients will receive oral Sorafenib, 400 mg twice daily. Sorafenib treatment will be continued until there is evidence of treatment failure (lack of efficacy resulting in tumour progression at any site determined by CT or MRI scan); there is a cure or complete response and/or the patient undergoes surgical resection, liver transplantation or ablative therapy; unacceptable toxicity occurs; or the patient requests an end to treatment. As published previously, doses may be delayed and/or reduced for clinically significant haematological toxicities and other toxicities or adverse events (AEs) related to study therapy. Dose reductions first to 400 mg/day and then to 400 mg every second day will be allowed, and if further dose reductions are required the patient should be discontinued. For non-haematological AEs other than skin toxicity, treatment will be interrupted for any grade 3 AE, and the dose subsequently reduced by one level. For skin toxicity, treatment will be interrupted for any grade 2 or grade 3 AE and a decreased dose frequency or level will be subsequently considered. The dose may be re-escalated once the toxicities or AEs have resolved [31].

Patients randomised to SIRT will receive SIR-Spheres at the patient-specific prescribed activity within 35 days after signing of informed consent form, and after the baseline assessment of their suitability for the procedure. The assessment comprises a hepatic angiogram, and a liver-to-lung shunt pre-assessment with Technetium-99 m (^99m^Tc)-labelled human serum albumin. The hepatic angiogram will determine the vascular anatomy of the liver in order to plan the optimal delivery of the SIR-Spheres. The ^99m^Tc lung-shunt study will assess the presence and degree of lung shunting from the liver. Patients randomised to SIRT, but who are found to be unsuitable for treatment will be included in the SIRT intention to treat analysis. The prescribed activity of SIR-Spheres® will be calculated based on the patient’s body surface area (BSA) model [32], or the partition model [33]. If the BSA method is used for dose calculation and the percentage lung shunting exceeds 20 % of the hepatic artery blood flow, as determined by ^99m^ Tc-scan, the partition model may be used to adjust the prescribed activity so that the radiation absorbed dose to the lungs does not exceed 20 Gy.

### Assessments

A quadriphasic contrast-enhanced spiral CT scan of the abdomen/pelvis will be performed at screening to diagnose HCC according to the American Association for the Study of Liver Diseases (AASLD) criteria [34], determine the extent of liver disease and to exclude extra-hepatic abdominal or pelvic metastases. A biopsy positive for HCC is required for diagnosis if the tumour does not fulfil the AASLD radiological criteria. A thoracic CT scan will be performed to exclude lung metastases. MRI scans will be used in lieu of CT scans in patients for whom CT scanning is not clinically feasible. Each of these CT series will be performed less than 28 days before informed consent is received. All radiology images in this trial will be centrally reviewed by treatment-blinded radiologists at the National Cancer Center Singapore.

All patients will be assessed by the schedule summarised in Table 2. Assessments are at 4-week intervals for the first three months, and then 12-week intervals thereafter. After study conclusion patients will be followed for survival or death at 12-week intervals.

**Table 2 Tab2:** SIRveNIB trial assessment schedule

Schedule	Screening/Baseline (Eligibility) Randomisation^a^	During Protocol Therapy					Study Conclusion	Post Study Conclusion Follow-Up
		Week 2^b^	Week 4	Week 8	Week 12	12-weekly thereafter	As appropriate^c^	12 weekly
Informed consent	X							
Demographics	X							
Medical and surgical history	X							
Concurrent illness	X							
Concomitant medications	X^d^	X^d^	X^d^	X^d^	X^d^	X^d^	X^d^	
Clinical assessment & physical examination • Height (Baseline only) • Weight • Blood pressure • Body temperature	X		X	X	X	X	X	
Performance status • ECOG	X		X	X	X	X	X	
Haematology • Leukocytes • Platelets • Haemoglobin • INR	X		X	X	X	X	X	
Hepatitis serology • Hep Bsag • Anti-HCV IgG • Hep B Core Antibody IgG (optional)	X^e^							
Renal function • Creatinine	X		X	X	X	X	X	
Liver function • AST/ALT • ALP • Total bilirubin • Albumin	X		X	X	X	X	X	
Pregnancy test (as appropriate)	X^f^							
Tumour marker • Serum AFP	X				X	X	X	
EQ-5D HRQoL	X		X	X	X	X	X	X
CT or MRI scan: chest/abdomen/pelvis^h, i^	X				X	X		
*SIRT-arm ONLY* • Hepatic angiogram • ^99m^Tc- MAA lung shunt study	X ^g^							
Response assessment					X	X	X	
*Sorafenib arm ONLY* • Toxicity assessment • Dose delay/modification		X^b^	X	X	X	X	X	
AE/SAE	AE/SAE for the Sorafenib arm will be recorded from the time of signing the ICF until 30 days after the final dose of Sorafenib, or until commencement of the next alternative therapy, whichever is earlier. AE/SAE for the SIRT arm will be recorded from the time of signing the ICF until 30 days post-SIRT regardless of causality and for a further 5 months thereafter if judged by the investigator to be causally related to SIRT or Sir-Spheres, or until commencement of the next alternative therapy, whichever is earlier. If the AE/SAE is a Sorafenib or SIRT related toxicity follow-up will continue until resolution.							
Survival								X

^a^Screening assessments performed within 28 days before signing of informed consent can be used to confirm eligibility

^b^Sorafenib arm only. Sorafenib patients contacted at Week 2 to assess treatment related toxicity and interrupt/modify the dose as necessary

^c^Disease progression, death, complete regression, unacceptable toxicity, patient responds to treatment and becomes eligible for surgical resection, liver transplantation or ablative therapy, lost to follow-up, patient’s request for withdrawal

^d^Concomitant medication to be recorded from screening up to 30 days post-study conclusion, or until commencement of the next alternative therapy, whichever is earlier

^e^If either the Hepatitis B Surface Antigen (Hep Bsag) test or anti-HCV IgG test is positive, the other test will be optional. Hepatitis B Core Antibody IgG test is optional

^f^Women of reproductive potential must have a negative pregnancy test before commencing treatment. Test to be repeated if pregnancy is suspected during the study

^g^Hepatic angiogram and ^99m^Tc-MAA lung shunt study to be performed after randomisation and prior to treatment commencement only for SIRT arm group

^h^The same radiological assessment method must be used throughout the study

^i^ Assessment for tumour response rate to be done every 12 weeks from date of randomisation until first evidence of disease progression

Study conclusion is defined as disease progression, death, complete regression, unacceptable toxicity, patient-undergoing surgical resection, liver transplantation or ablative therapy due to a sufficient response with therapy, loss to follow-up, or patient’s request for withdrawal.

### Outcome measures

The primary endpoint of the SIR*ve*NIB trial is overall survival (OS). Secondary endpoints include: time to progression (TTP), progression-free survival (PFS), overall and in the liver; tumour response rate (assessed by Response Evaluation Criteria in Solid Tumours [RECIST] version 1.1) [35]; disease control rate; health-related quality of life (HRQoL); safety and toxicity; and liver resection rate and liver transplantation rate.

### Outcome definitions

OS – the time from the date of randomisation to death from any cause.TTP – the time from the date of randomisation to tumour progression at any site in the body.PFS at any site – time from the date of randomisation to tumour progression at any site in the body or death, whichever is earlier.PFS in the liver –time from the date of randomisation to tumour progression in the liver or death whichever is earlier.Tumour response rate is the number of patients whose best overall response rate (best tumour response over the whole study between randomisation and the last tumour assessment) is partial response (PR) or complete response (CR), divided by the total number of patients in the analysis population.Disease control rate – the number of patients whose best overall response is PR, CR or stable disease (SD), divided by the total number of patients in the analysis population.HRQoL assessed using the EQ-5D questionnaire.Adverse events will be reported according to National Cancer Institute criteria (National Cancer Institute Common Terminology criteria for Adverse Events [NCI CTCAE] Version 4.02) [36].

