As the SIRT therapy is a local treatment, treatment effect of progression in the liver as the first event will be investigated using a competing risk analysis. In this analysis death or progression outside the liver as the first event will be considered as a competing risk for liver progression. The method of Gray [40] will be used to compare groups with hazard ratios and 95 % CI estimated from the proportional hazards approach detailed by Fine and Gray [41]. Time to liver progression in the two groups will be displayed using cumulative incidence curves.

Toxicity will be reported according to NCI CTCAE Version 4.02 criteria.

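### PFS in the liver needs liver scans after extrahepatic-only progression, but scanning stops at first progression at any site, so the endpoint runs too long for those patients

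*Protocol article*

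**What the plan says.** Under Outcome measures the article lists as secondary endpoints "progression-free survival (PFS), overall and in the liver". Under Outcome definitions, PFS in the liver is counted from randomisation to "tumour progression in the liver or death whichever is earlier". Extrahepatic progression is not an event for this endpoint, and no rule is given for it.

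Under Assessments, footnote i of Table 2, attached to the imaging row ("CT or MRI scan: chest/abdomen/pelvis^h, i"), reads: "Assessment for tumour response rate to be done every 12 weeks from date of randomisation until first evidence of disease progression". That row is marked at baseline, week 12 and 12-weekly during protocol therapy. It is blank at study conclusion and in the follow-up after it.

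The text under Table 2 adds: "Study conclusion is defined as disease progression, death, complete regression, unacceptable toxicity", among other reasons, with no restriction by site. Follow-up then narrows: "After study conclusion patients will be followed for survival or death at 12-week intervals". Table 2 adds EQ-5D to that follow-up, but no imaging.

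Under Statistical analyses, a separate analysis takes liver progression as the first event, and "death or progression outside the liver as the first event will be considered as a competing risk for liver progression". It uses Gray's test, the Fine-Gray model and cumulative incidence curves.

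**The concern.** The definition asks for something that the schedule does not collect. Once a patient has progressed outside the liver only, the liver is no longer scanned under the plan, but the date of death is still recorded. Applied literally, the endpoint passes over any liver progression in between and takes death as the event. The recorded time is then too long.

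If the share of extrahepatic-first failures differs between arms, the error differs too, and the hazard ratio moves in favour of the arm with more of them. The article itself describes SIRT as a local treatment, so a liver-specific result is a natural place to look for benefit. An apparent benefit could arise there with no difference in liver control.

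**Working it through.** **Step 1: definition against schedule**

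| First event | Can liver PFS be observed? |
|---|---|
| Liver progression, alone or with extrahepatic progression at the same scan | Yes |
| Death before any progression | Yes |
| Extrahepatic progression only | No: liver progression is unseen, death is seen |

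Footnote i is worded for tumour response, but it sits on the imaging row, and the blank cells at and after study conclusion show independently that scanning stops. Nothing limits the stopping event to the liver: TTP, PFS at any site and the sorafenib stopping rule all refer to any site.

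There is no figure in the plan to reproduce for this endpoint. The next two steps show direction and possible size only. All their inputs are assumptions.

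**Step 2: equal liver-progression hazards**

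Assumed per month: liver progression λL = 0.10 in both arms; death λD = 0.02 before and 0.06 after first progression; extrahepatic progression λE as in the table. Share of patients with extrahepatic progression first = λE / (λL + λE + λD). For example, 0.01/0.13 = 8 %, 0.02/0.14 = 14 %, 0.06/0.18 = 33 %.

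- True liver PFS = min(liver progression, death).
- As written = time of death if extrahepatic progression comes first, otherwise the true value.
- Cox hazard ratio SIRT/sorafenib to 36 months, simulated with at least 200,000 patients per arm. Ranges span repeated runs.

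| λE, SIRT vs sorafenib | Extrahepatic-first share | True HR | HR as written |
|---|---|---|---|
| 0.01 vs 0.005 | 8 % vs 4 % | 1.01 | 0.97 |
| 0.04 vs 0.02 | 25 % vs 14 % | 1.02–1.04 | 0.93–0.94 |
| 0.06 vs 0.03 | 33 % vs 20 % | 1.03–1.04 | 0.92–0.93 |
| 0.06 vs 0.02 | 33 % vs 14 % | 1.05–1.06 | 0.88–0.89 |
| 0.02 vs 0.02 | 14 % vs 14 % | 1.00 | 1.00 |
| 0.02 vs 0.03 | 14 % vs 20 % | just below 1.00 | 1.04 |

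The true ratio exceeds 1 in the first four rows because death is assumed more likely after progression and SIRT is assumed to have more extrahepatic progression.

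**Step 3: would censoring at extrahepatic progression cure it?**

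A second set-up makes the true HR 1.00 by construction: median time to liver progression 5 months and to death 12 months in both arms, with extrahepatic-first shares (of first progressions) of 10 % in one arm and 20, 30 or 40 % in the other. A shared gamma frailty makes the risks positively correlated.

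| Handling | Frailty variance | HR at 20 / 30 / 40 % |
|---|---|---|
| Carried to death (literal) | 0 | 0.91 / 0.84 / 0.77 |
| Carried to death (literal) | 1 | 0.96 / 0.92 / 0.88 |
| Censored | 0 (independent) | 1.00 / 1.00 / 1.00 |
| Censored | 0.5 | 0.97 / 0.94 / 0.90 |
| Censored | 1 | 0.96 / 0.91 / 0.86 |

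Censoring removes the bias only if liver and extrahepatic risks are independent. With positive correlation it is biased in the same direction as the literal reading.

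**Step 4: size against sampling error**

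Assume about 330 liver-PFS events among 360 patients. The standard error of the log HR is about 2/√330 = 0.11. At the mild end of Step 2 the shift is ln(0.97/1.01) = −0.04, about 0.4 standard errors. At the strong end it is ln(0.88/1.06) = −0.19, about 1.7 standard errors.

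**The case against.** The strongest reply has four parts.

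- **The gap concerns a subset.** Liver PFS is observable for everyone who progresses in the liver first, progresses in both places at one scan, or dies first. The Background says that HCC often kills before extrahepatic metastases develop, and eligibility excludes nearly all extrahepatic disease at entry. The subset may be small. This stands: a reader might infer that the endpoint cannot be observed at all, and the documents do not support that.
- **The bias depends on a handling rule that the article does not state.** A censoring rule for a secondary endpoint is commonly left to the SAP, so its absence is no fault. With the Step 2 hazards and censoring at extrahepatic progression, the HR is 1.00 to 1.01. This stands in part. A rule can be added, but it cannot recover scans that were not scheduled, and Step 3 shows that censoring is safe only under independence.
- **The favoured arm is not known.** A reader might infer that the endpoint flatters SIRT because SIRT treats only the liver. That is plausible, but the article reports no extrahepatic-first rates. With equal hazards the effect vanishes, and with more such failures on sorafenib it reverses. This stands.
- **The competing-risks analysis already covers the liver question.** It fits the scan schedule, because it needs nothing after first progression. A reader might infer that the Fine-Gray ratio is itself faulty because it responds to the competing hazards. That response is a property of the subdistribution hazard, not an error in the plan. This stands too, but the analysis neither redefines nor replaces PFS in the liver, which remains a listed and defined endpoint.

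**Conclusion.** The contradiction holds: the definition keeps patients with extrahepatic-only progression at risk, and the schedule stops looking at their livers while still counting their deaths. Read literally, liver PFS is too long for these patients, and the comparison leans towards the arm with more of them.

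Size and direction are conditional. Under the hazards assumed above with more extrahepatic progression on SIRT, the HR as written is about 0.97 to 0.88 against a true 1.01 to 1.06. The documents support neither a particular value nor a claim that SIRT must benefit. The matter is confined to a secondary endpoint; overall survival is unaffected. It is worth correcting because the remedy is cheap and the final analysis was still awaiting 266 deaths at the article's Trial status.

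**What to change.** 1. Make the first-event competing-risks analysis already planned under Statistical analyses the liver-specific comparison, in place of PFS in the liver.
2. Beside the cumulative incidence curves, report cause-specific Cox hazard ratios for liver progression and for extrahepatic progression or death. They supplement the Fine-Gray ratio and do not correct it. Together they show whether a difference comes from liver control or from the competing events.
3. Do not present a Kaplan-Meier curve of liver PFS as defined unless liver imaging did continue after extrahepatic progression.

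The cost is two extra Cox models and one relabelled secondary endpoint. No new data are needed.

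One limit remains. Study conclusion also covers reasons other than progression, such as toxicity or complete regression, and the imaging row is blank after these as well. That gap is wider than this endpoint, and the change above does not close it.
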